#### Missing data

If required, we will use multiple imputation to account for missing data in analyses that cannot handle occasional missing values [42]. If there are missing data for the primary outcome, we will either: (i) substitute from the fortnightly sports participation data, or (ii) use multiple imputation if there are > 15% missing outcome data. If there are missing data for the secondary outcomes, we will use multiple imputation if there are > 15% missing outcome data.

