#### Primary outcome measure

For the primary outcome, return to sport is determined based on a composite of answers to 4 questions (Additional file 1), which we have refined based on our previous research [19, 35, 36].

To be classified as returned to the preinjury sport *and* level (i.e. *yes* for the primary outcome), participants must have answered *I have returned to the same sport as before injury* to question 1, AND *I have returned to full training and modified competition* or *I have returned to full training and full competition* to question 2, AND selected the same sport as they played preinjury at question 3, AND selected the same level as they played before injury at question 4 (to ensure accuracy, we cross-check answers to question 3 and question 4 at 12 months, against the baseline data).

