#### Secondary outcome measures: *sports participation*

Participants self-report the activity or activities (participants can register up to 3 separate activities) they participated in during the registration period (preceding two weeks). Participants select an activity from a list of 19 sports; there is also an option to specify an unlisted activity. Participants report the number of minutes they participated in each activity during the registration period, and the total number of physical activity sessions including, but not limited to knee rehabilitation sessions, active recreation, training/practice and competition.

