### Sample size calculation

There are no trials of psychological support interventions aimed to help athletes return to sport following sports injury, so it is difficult to accurately estimate the expected effect size for our trial. We calculated the same size required to detect a between-group difference in return to preinjury sport rate of 20% at 1 year. We assumed a base return to sport rate of 33%, [39] a two-sided alpha of 0.05, beta of 0.2, and a drop-out rate of 15%. The required sample size is 222 participants (111 in each group).

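### Missing primary outcomes may be filled from fortnightly records that, as described, lack two of the endpoint's four components, and the multiple-imputation trigger sits exactly at the planned drop-out

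*Protocol article*

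**What the plan says.** All references are to the protocol article.

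- *Missing data*, rule for the main endpoint: "we will either: (i) substitute from the fortnightly sports participation data, or (ii) use multiple imputation". The second route is limited to losses above 15%. No order between the two routes is given, and no rule for turning a fortnightly record into a yes or no.
- *Missing data*, opening sentence, with no threshold: "If required, we will use multiple imputation to account for missing data in analyses that cannot handle occasional missing values".
- *Primary outcome measure*: four answers must all be met. Question 1 is same sport by self-report. Question 2 is full training with modified or full competition. Question 3 is the same named sport. For question 4 the participant must have "selected the same level as they played before injury at question 4".
- *Secondary outcome measures: sports participation*: participants name up to three activities. "Participants report the number of minutes they participated in each activity during the registration period". They also give one session total that pools rehabilitation, recreation, training and competition.
- *Sample size calculation*: "a two-sided alpha of 0.05, beta of 0.2, and a drop-out rate of 15" per cent, with a control rate of 33% and a difference of 20 points.

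**The concern.** The substitute source does not measure what it is meant to replace. Minutes logged in the old sport are compatible with full return, with modified training only, and with play at a lower level. Only the first counts as a success. Filling some outcomes this way would give the primary endpoint two definitions, depending on who answered the 12-month questions. Single substitution also treats a guess as an observation, so its uncertainty does not reach the confidence interval.

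The trigger adds a second weakness. Imputation, the method that could use the fortnightly data properly, is reserved for losses above the figure the trial was sized to tolerate. At or below that figure, an outcome that cannot be substituted has no clearly stated handling, because the threshold-free opening sentence is not reconciled with the 15% rule. One participant more or less can change the primary method.

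**Working it through.** **1. Endpoint against substitute source**

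| Component | Needed for success | In the fortnightly record as described |
|---|---|---|
| Q1, Q3 | same sport | yes (activity name, minutes) |
| Q2 | full training plus modified or full competition | no (one pooled session total) |
| Q4 | same level | no level item |

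No minutes in the old sport around 12 months implies failure on Q1 and Q3, so a no is reasonable. Some minutes leave Q2 and Q4 unknown.

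**2. The plan's own sample size**

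Inputs: 33% vs 53%, two-sided 0.05, power 80%, 15% drop-out. With pooled variance and no continuity correction,

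n = [1.960·√(2·0.43·0.57) + 0.842·√(0.33·0.67 + 0.53·0.47)]² / 0.20²,

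which is just over 95.0, so 96 per arm. Then 96 × 1.15 = 110.4, giving 111 per arm and 222 in total, as stated. (96/0.85 gives 113 per arm, 226 in total.)

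**3. The trigger**

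0.15 × 222 = 33.3. With 33 missing, 33/222 = 14.9% and imputation is not triggered. With 34 missing, 34/222 = 15.3% and it is. If missingness is binomial, the chance of at least 34 missing is:

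| True missing rate | P(at least 34 of 222) |
|---|---|
| 10% | 0.008 |
| 12% | 0.082 |
| 15% | 0.476 |
| 18% | 0.872 |
| 20% | 0.970 |

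**4. Effect of miscoding, equal missingness**

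Assumptions, none from the documents: a fraction m = 0.15 is missing in each arm, all of them have a usable fortnightly record, a share q of the non-returners among them is coded as returned, and no returner is miscoded. The observed rate is p + m(1 − p)q, so the difference is multiplied by (1 − mq). Power is for 111 per arm.

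| q | Control | Experimental | Difference | Power |
|---|---|---|---|---|
| 0 | 33.0% | 53.0% | 20.0 points | 0.86 |
| 0.2 | 35.0% | 54.4% | 19.4 points | 0.83 |
| 0.4 | 37.0% | 55.8% | 18.8 points | about 0.81 |
| 1 (extreme) | 43.1% | 60.1% | 17.0 points | 0.72 |

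For scale, the standard error of the difference is √[(0.33·0.67 + 0.53·0.47)/111] = 0.065, or 6.5 points.

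**5. No true effect, unequal missingness**

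Let both arms have p = 0.33, with 20% missing in control and 10% in experimental (assumed). Substitution bias = (0.10 − 0.20) × 0.67 × q, which is −1.3 points at q = 0.2 and −2.7 points at q = 0.4. With equal missingness it is zero.

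Leaving the missing out instead, with non-returners r times as likely to be missing (risk ratio), returners are missing at rate a = m/(0.33 + 0.67r) and the observed rate is 0.33(1 − a)/(1 − m). For r = 2 this gives 34.5% − 36.3% = −1.8 points. For r = 3 it gives 35.1% − 37.7% = −2.6 points.

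**The case against.** Several points on the other side carry weight.

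- A reader might infer that imputation will never be used at the planned loss. The text does not support that. The 15% is a planning figure, and if it is the true rate the chance of crossing the trigger is about 48%. Non-response by people who stay in the trial would raise that chance. The opening sentence also permits imputation without a threshold.
- A reader might infer that people in modified training or at a lower level will be counted as returned. The article gives no coding rule, so this is a possibility and not a stated plan.
- A reader might infer that the method will be picked after seeing results. The natural reading is graded: substitute up to 15%, impute above. The analyst is also blinded to allocation. What remains open is narrower, namely whether the 15% is counted before or after substitution.
- Unequal missingness is not shown. Both arms use the same app for data collection, receive the same number of notifications and are followed up by text message. The experimental arm also receives task reminders, so a difference is possible, but no more than that.
- The questionnaires are in Additional file 1, which is not shown. The fortnightly form may hold more items than the article lists.
- Substitution can reach only people who still supply fortnightly records, so applying q to all 15% overstates the distortion.

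All of these stand and limit the size and certainty of the point. None of them supplies level or competition status to the substitute source as described.

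**Conclusion.** The point holds in a limited form. As the article describes it, the fortnightly registration cannot establish Q2 or Q4 for anyone who logs the preinjury sport, and the imputation trigger coincides with the planned loss, so one participant separates two primary methods. With equal missingness and 20–40% miscoding the bias is toward the null and small: 0.6 to 1.2 points off a 20-point difference, well under one standard error, with power still at or above the planned 80%. A bias of about 1–3 points under no effect depends wholly on an assumed imbalance in missingness and is at most about 0.4 of a standard error. This should be fixed because it governs the primary endpoint and the better method costs little. It does not threaten the trial's validity.

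**What to change.** In *Missing data*, remove the 15% trigger for the primary outcome and state one method: multiple imputation whenever any primary outcome is missing. Use the fortnightly sport and minutes records and the earlier ACL-RSI and motivation scores as auxiliary variables. The fortnightly data then inform the missing value without being taken as equal to it. Keep two labelled sensitivity analyses: substitution from the fortnightly data, with its coding rule stated (which registration period counts, and how level and competition are settled), and missing counted as not returned. Reconcile the opening *if required* sentence with this rule.

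The cost is a change of wording and a little extra programming. The auxiliary data are already being collected, and neither the sample size nor trial conduct changes. It should be settled before outcome data are examined.

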#### Planned secondary analyses: time-varying analyses

We will compare psychological readiness to return to sport (ACL-RSI), motivation to return to sport, self-reported knee function (SANE and IKDC), sports participation and new knee injury between treatment groups using generalised estimating equations. Group, clinical site, and assessment time point will be included as fixed factors. If baseline values were collected, we will also include the baseline value in the relevant model as a covariate. For continuous variables, we will calculate mean difference and 95% confidence intervals. For dichotomous variables, we will calculate the odds ratio and 95% confidence intervals.

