#### Planned secondary analyses: cross sectional analyses

For self-efficacy (K-SES) and quality of life (ACL-QoL), we will use generalised estimating equations for comparisons at 12 months (model 1) and 24 months (model 2) between treatment groups. Group and current participation in preinjury sport will be included as fixed factors. We will calculate mean difference and 95% confidence intervals. In model 2, we will include the 12-month values as a covariate.

For adherence, we will compare the median number of rehabilitation sessions completed per person (i) with the physiotherapist, (ii) at home, (iii) at a gymnasium between the treatment groups using generalised estimating equations.

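### The 15% trigger for imputing secondary outcomes lets the amount missing choose the method, although the amount missing does not show that available-case GEE is valid

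*Protocol article*

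**What the plan says.** The Missing data section of the protocol article has a general sentence and then a specific rule. The general sentence is "If required, we will use multiple imputation to account for missing data in analyses that cannot handle occasional missing values". The rule for secondary outcomes is "If there are missing data for the secondary outcomes, we will use multiple imputation", on the condition that more than 15% of the outcome data are missing.

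The analyses to which the rule applies come under two later headings.

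- **Time-varying analyses.** ACL-RSI, motivation, SANE, IKDC, sports participation and new knee injury are compared by GEE. On the model terms: "Group, clinical site, and assessment time point will be included as fixed factors", and "If baseline values were collected, we will also include the baseline value in the relevant model as a covariate". Table 3 lists the baseline variables; ACL-RSI, motivation and SANE are not among them.
- **Cross sectional analyses.** For K-SES and ACL-QoL, "we will use generalised estimating equations for comparisons at 12 months (model 1) and 24 months (model 2) between treatment groups". The listed terms are group and current participation in the preinjury sport, and for the later model "In model 2, we will include the 12-month values as a covariate". Baseline K-SES is in Table 3 but is not listed as a covariate in the 12-month model.

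Neither heading mentions weighting for non-response. Read together, the sections leave GEE on whatever was returned when 15% or less is missing.

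**The concern.** Whether an available-case analysis is biased depends on why data are missing. The fraction missing limits how large the bias can be, but it does not show that the analysis is valid. Unweighted GEE needs one of three things: data missing completely at random; missingness that depends only on covariates in the model; or, approximately and for repeated continuous outcomes, a working correlation close to the truth. The 15% line tests none of them.

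The rule also makes the method depend on the data. Two secondary outcomes on either side of the line would be analysed under different missing-data assumptions.

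At stake are the estimates for outcomes close to the app's proposed mechanism and for its possible harm. Arm-related non-response is plausible but not shown. The Blinding section accepts that participants may not remain blind, and the Data collection section has one app deliver the intervention and collect the research data.

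**Working it through.** **1. Where the line falls.** Inputs: 222 participants and 15% drop-out (Sample size calculation); trigger strictly above 15% (Missing data). 0.15 × 222 = 33.3. If the fraction is counted over all randomised, 33/222 = 14.9% gives no imputation and 34/222 = 15.3% gives imputation. The planned drop-out therefore sits on the line. (The figure of 222 itself reproduces: 96 per arm for 33% vs 53%, and 96 × 1.15 = 110.4, rounded up to 111. The point does not depend on it.)

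**2. Single-visit contrast.** The protocol gives no figure for this bias, so the inputs are assumptions: SD 20, correlation r = 0.7 between the outcome and an earlier score, no true difference, and logistic missingness on the standardised earlier score. Let m be the fraction missing and d the mean shortfall, in SDs, of non-responders on the earlier score. The responders' mean in that arm is shifted by

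SD × r × m/(1 − m) × d.

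| Scenario | Calculation | Bias (points) |
|---|---|---|
| 14% missing in each arm, score-driven in one arm, slope 1 (d = 0.76) | 20 × 0.7 × 0.163 × 0.76 | 1.7 |
| Same, slope 1.5 (d = 1.01) | 20 × 0.7 × 0.163 × 1.01 | 2.3 |
| 18% vs 10%, slope 1 in both arms (d = 0.72 and 0.82) | 14 × (0.220 × 0.72 − 0.111 × 0.82) | 0.9 |
| Same slope and same rate in both arms | the two shifts cancel | about 0 |

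Large simulations of the first two rows gave 1.6 to 1.8 and 2.2 to 2.3, so the range is 1.6 to 2.3 points.

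With 111 × 0.85 ≈ 94 per arm, SE = 20 × √(2/94) = 2.92. The one-arm bias is 1.64/2.92 = 0.6 to 2.3/2.92 = 0.8 SE, and the 18% vs 10% bias is 0.92/2.92 = 0.3 SE. A nominal 5% test then rejects about 9% to 12% of the time, or about 6%. In SD units the biases are 0.08 to 0.12 and 0.05. Use those for K-SES, which runs from 0 to 10.

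**3. Repeated continuous outcomes.** Simulated GEE at the last visit: N = 222, 4 visits, within-person correlation 0.6 (assumed), no true effect, about 14% missing, 400 runs per scenario.

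| Missingness | Working correlation | Bias (SD) | Type I error |
|---|---|---|---|
| Completely at random | independence / exchangeable | 0.015 / 0.015 | 0.052 / 0.045 |
| Depends on group only | independence / exchangeable | 0.007 / 0.002 | 0.065 / 0.075 |
| Previous score, same in both arms | independence / exchangeable | 0.001 / 0.001 | 0.052 / 0.050 |
| Previous score, opposite by arm | independence | 0.151 | 0.205 |
| Previous score, opposite by arm | exchangeable (correct) | −0.006 | 0.050 |
| Opposite by arm, AR(1) truth | independence | 0.111 | 0.145 |
| Opposite by arm, AR(1) truth | exchangeable (misspecified) | −0.012 | 0.075 |

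The Monte Carlo SE of the type I error is about 0.011. For these outcomes the exposure comes almost entirely from an independence working correlation.

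**4. Which outcomes lack this protection.** The 12-month K-SES and ACL-QoL models have one record per person, so a working correlation has no earlier score to draw on, and no baseline or earlier score is listed as a covariate. Step 2 describes these models most closely. For the binary injury outcomes, a correct working correlation does not in general make GEE valid under missing at random.

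**The case against.** A reader might infer that GEE below the line is valid only if data are missing completely at random. The documents do not support that. Missingness that depends on group, site, time, a collected baseline value or, in the 24-month models, the 12-month value is covered by the stated models. Step 3 shows that a reasonable working correlation removes nearly all the bias for repeated continuous outcomes.

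A reader might also apply the 1.6 to 2.3 points to ACL-RSI. That figure belongs to a single-visit contrast that ignores earlier visits. The time-varying models list no group-by-time term, so the stated group effect is pooled over visits. A further simulation of the step 2 scenarios, with the five ACL-RSI visits, gave pooled biases of at most 0.06 points with a correct exchangeable correlation, at most 0.12 with a misspecified one, and 0.3 to 0.8 (one-arm mechanism) with independence. The working correlation may be fixed in an analysis plan that is not shown, so its absence is no fault here.

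Three other objections carry some weight. The general sentence keeps imputation open where required, but it covers analyses that cannot handle occasional gaps, and the specific 15% rule follows it. Questionnaire reminders, text-message follow-up and, for injury reports, contact or record review should reduce missing data, but they do not justify the cut-off. Non-response that differs by arm is assumed; the protocol says only that blinding cannot be relied on.

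**Conclusion.** The point holds in a limited form. The protocol fixes a percentage trigger that chooses the analysis without bearing on its validity, and the planned 15% drop-out sits on that trigger. The consequence is real but modest. The 12-month K-SES and ACL-QoL comparisons and the binary injury outcomes are the most exposed. Repeated continuous outcomes are little affected unless an independence working correlation is used.

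For a single-visit contrast the bias is about 0.6 to 0.8 SE if score-driven non-response occurs in one arm only, about 0.3 SE with 18% vs 10% missing, and about zero if pattern and rate are equal. These sizes rest on the assumed SD, correlations and strength of missingness, none of which the protocol gives. They were worked out for a continuous outcome, and no size was computed for the injury outcomes. Severity is minor to moderate, because only secondary outcomes are affected.

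**What to change.** Delete the 15% condition for secondary outcomes and state an analysis that is valid under missing at random whatever the percentage missing.

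- **K-SES and ACL-QoL at 12 and 24 months, and binary and count outcomes:** multiple imputation including arm, site, collected baseline values (including baseline K-SES) and earlier reports.
- **Repeated continuous outcomes (ACL-RSI, IKDC, SANE and similar):** either a likelihood-based mixed model or the planned GEE after the same imputation.
- **Sensitivity analysis:** available-case GEE.

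The fortnightly reports and the scheduled earlier questionnaires already supply the predictors, so no new data are needed. The cost is a change of wording and slightly more programming.

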#### Reclassifying variables

For new knee injuries, we plan to classify the collected data into three dichotomous variables for analysis: (i) new knee problem (based on all complaints), (ii) new ACL injury (either knee), (iii) new knee injury treated with surgery. The trial co-ordinator will check all injury registration reports as they are completed and returned by participants. If additional information (e.g. injury diagnosis and treatment) is required, a blinded researcher will contact the participant by phone or text message, and/or review the participant’s medical record (Additional file 1).

#### Data security

All data are managed according to the European Union General Data Protection Regulation. A password-protected electronic record of all trial activities will be maintained according to University requirements. Patient-reported data are collected electronically, coded according to the participant’s unique study identification number, and stored electronically on a password-protected University server. Clinical follow-up data are collected using an electronic template, coded according to the participant’s unique study identification number, and stored electronically on a password-protected University server.

Identified data (including personal information; the coding list will be stored separate to the identified data) will be stored at the co-ordinating University for 10 years after completion of the study. Coded data and statistical code for generating results will be deposited on the Swedish National Data Service server within 6 months of study completion, and will be available indefinitely.

#### Data sharing

We plan to share coded individual participant data for the primary and secondary outcomes, and statistical code, with researchers whose proposed use has been approved by an independent review committee. Individual participant data will only be shared for the purpose of individual participant data meta-analysis. Data must be requested through the Swedish National Data Service (http://snd.gu.se).

### Statistical analysis plan

For the main analysis, we will use the intention-to-treat principle. An independent statistician, blinded to group allocation, will perform the analyses using the coded database. The criterion for statistical significance will be < 0.05.

To assess baseline comparability of treatment groups, we will compare baseline characteristics (Table 3) using generalised estimating equations. If there are major imbalances in baseline characteristics, we will attempt to rebalance the groups using multivariable regression modelling.

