### Eligibility criteria

Participants who meet the following criteria will be included in the trial:
Age 15 years to 30 years at the time of ACL injuryUnilateral primary ACL rupture (diagnosed by clinical examination and/or MRI)Time between injury and ACL reconstruction not more than 12 monthsPlaying contact pivoting or non-contact pivoting sport at least twice per week prior to ACL injuryIntend to return to sport following ACL reconstructionNormal/healthy contralateral kneeFluent in written and spoken Swedish language

Participants with the following will be excluded from the trial:
Medial collateral ligament or lateral collateral ligament injury requiring surgeryPosterior cruciate ligament injuryMeniscus injury and/or treatment requiring alteration to usual rehabilitation careArticular cartilage injury and/or treatment requiring alteration to usual rehabilitation carePrevious ACL injury to either kneeInjury to either lower limb that required medical care during the 12 months prior to index ACL injuryOther injury or illness that could affect knee rehabilitationTaking medication for mental health problems

We recruit young, pivoting sport athletes who desire to return to sport, because the intervention is tailored to address the mental challenges these athletes typically report [13–17]. Participants must have sufficient Swedish language comprehension because the intervention is only available in Swedish. Previous experience of ACL injury, [18] and social and contextual factors, including age and desire to return to sport, [8, 19, 20] may also influence returning to sport. Our eligibility criteria will help minimise the confounding effect of injury history, age and desire to return to sport on the trial results.

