Limb symmetry index is calculated using the formula: $$ \frac{involved\ limb}{uninvolved\ limb}\times 100 $$; ACL, anterior cruciate ligament

**Table 3 Tab3:** Baseline participant characteristics

Variable	Aggregation
Time from injury to surgery	median (IQR)
Age at injury	mean (SD)
Sex	
Female	n (%)
Male	n (%)
Primary occupation	
Student	n (%)
Desk work	n (%)
Manual work	n (%)
Heavy manual work (e.g. construction)	n (%)
Unemployed	n (%)
Preinjury sports participation	
Contact, pivoting sport	n (%)
Non-contact, pivoting sport	n (%)
Return to sport goal	
Return to same sport	n (%)
Return to different sport	n (%)
Return to sport expectations	
Within 1 month	n (%)
Within 6 months	n (%)
Within 12 months	n (%)
After 12 months	n (%)
IKDC subjective knee form [28] score	mean (SD)
General Self-efficacy Scale [33] score	mean (SD)
Knee Self-Efficacy Scale [25] *Future domain*	mean (SD)
Hospital Anxiety & Depression Scale [34] score	mean (SD)

*IQR* interquartile range, *SD* standard deviation, *IKDC* International Knee Documentation Committee

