#### Primary analysis

To address the primary aim, we will compare the rate of returning to the preinjury sport and level at 12 months between the treatment groups. We will calculate the odds ratio and 95% confidence interval using generalised estimating equations. Group and clinical site will be included as fixed factors in the model.

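### Extra covariates would be chosen because the arms happen to differ on them, not because they predict return to sport, and no prognostic baseline variable is fixed in the primary model

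*Protocol article*

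**What the plan says.** All references are to the protocol article.

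- Statistical analysis plan, first step: "To assess baseline comparability of treatment groups, we will compare baseline characteristics (Table 3) using generalised estimating equations". Second step: "If there are major imbalances in baseline characteristics, we will attempt to rebalance the groups using multivariable regression modelling". The word *major* has no threshold, no covariate is named, and the text does not say whether the rebalanced model replaces the primary one or stands beside it.
- Primary analysis: "We will calculate the odds ratio and 95% confidence interval using generalised estimating equations", and "Group and clinical site will be included as fixed factors in the model". No baseline characteristic is in this model.
- Planned secondary analyses (time-varying): "If baseline values were collected, we will also include the baseline value in the relevant model as a covariate". Baseline adjustment is therefore prespecified for these secondary models.
- Eligibility criteria: the article itself says that "social and contextual factors, including age and desire to return to sport, [8, 19, 20] may also influence returning to sport".
- Table 3 (in Outcomes) records the return-to-sport goal, with "Return to different sport" as one of its two categories. Under Primary outcome measure, a success requires, among other answers, "I have returned to the same sport as before injury". The inclusion criterion asks for an intention to return to sport without tying it to the same sport.

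**The concern.** Methods describes 1:1 allocation in blocks of 6, stratified by site, and the concealment section describes one envelope opened per consenting participant. The sequence-generation section uses the term cluster randomisation, but what it describes is a separate schedule for each site. Allocation is thus individual within site, and any baseline difference is chance. Comparing the arms at baseline then tells the analyst nothing about which variables should be in the model.

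A covariate helps the primary analysis when it predicts the outcome. The stated rule admits it when it happens to differ between arms, so a strong predictor that is well balanced stays out and a weak one that is imbalanced goes in. Two things are at stake: power that prespecified adjustment would give, and a primary odds ratio whose meaning is settled in advance.

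**Working it through.** **1. The plan's own figure.** Inputs from Sample size calculation: 33% versus 53%, two-sided alpha 0.05, power 80%, drop-out 15%. Pooled two-proportion formula, mean rate 0.43:

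n = [1.960·√(2·0.43·0.57) + 0.842·√(0.33·0.67 + 0.53·0.47)]² / 0.20² = 95.0005, rounded up to 96 per arm.

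96/0.85 = 112.9, so 113 per arm (226 in total); 96 × 1.15 = 110.4, so 111 per arm (222 in total). The stated 222 is reproduced, and the covariate rule does not alter it. After drop-out 111 × 0.85 = 94.35 per arm remain, with power 79.7%.

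**2. How often the rule selects.** Assume that *major* means p < 0.05. Any one covariate then enters with probability about 0.05 under correct randomisation (4.0% to 5.5% in the simulations below), whatever its prognostic strength. Table 3 lists 11 characteristics. If they were also independent, at least one would trigger with probability 1 − 0.95^11 = 43% (34% for 8, 46% for 12). Both conditions are assumptions: the 0.05 in the article is its general significance criterion, and several Table 3 scales are likely to be correlated.

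**3. Power.** Simulation with logistic models and Wald tests, 94 per arm, 5,000 runs per row, overall rates held at 33% and 53%, site not simulated. For the goal variable, success among those aiming for a different sport is assumed to be 3% in both arms.

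| Assumed covariate | Unadjusted | Added only if p < 0.05 at baseline | Prespecified |
|---|---|---|---|
| Different-sport goal in 5% | 78.9% | 79.0% | 81.0% |
| in 10% | 79.1% | 79.5% | 82.9% |
| in 20% | 79.4% | 80.5% | 87.0% |
| Continuous, log-odds 0.5 per SD | 78.8% | 79.1% | 81.3% |
| 1.0 per SD | 79.1% | 79.9% | 85.6% |
| 1.5 per SD | 78.0% | 79.6% | 90.3% |

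The triggered rule gains 0.1 to 1.6 points; prespecification gains 2.1 to 12.3. The Monte Carlo standard error of one entry is about √(0.8·0.2/5000) = 0.6 points.

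**4. Which odds ratio.** Unadjusted: (0.53/0.47)/(0.33/0.67) = 2.29. Holding these overall rates and conditioning on a perfectly balanced normal covariate with log-odds 0.5, 1.0 or 1.5 per SD, the odds ratio is 2.40, 2.71 or 3.21. No bias is involved; these are different quantities.

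**5. Type I error.** With both arms at 33% and one covariate, the triggered rule rejected in 4.5% to 5.1% of runs. A check with 11 covariates gave 4.7%.

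**The case against.** The case for leaving the text alone has real parts.

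- Site, the stratification factor, is fixed in the primary model. The statistician is independent and blinded, and the trigger looks at baseline data, not outcomes. This limits deliberate choice of a favourable model, but it does not stop chance imbalance from choosing the covariates.
- The article does not say that the rebalanced model replaces the primary one. That is correct, and the claim here is only that it could.
- An article commonly leaves covariate lists to the analysis plan. It does, but here the article states a selection rule, and the rule is the problem.
- The goal variable is not barred. Under the rule it enters if imbalanced, which is the difficulty.
- Adjustment has a price. The odds ratio becomes conditional, and in a logistic model its interval does not generally narrow even though power rises. This stands, so the gain should not be described as free precision.

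A reader might infer two stronger things, and neither is supported. The first is that the two-step rule breaks the nominal error rate: step 5 shows no inflation, although a free choice among several models was not simulated.

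The second is that the rule costs the trial the power lost to participants aiming for a different sport. If 10% (20%) had that goal and could not succeed, and 33%/53% applied only to the rest, the rates would be 29.7%/47.7% (26.4%/42.4%) and power at 94.35 per arm would fall from 80% to 72% (64%). That is a matter of eligibility and base rate. Perfect conditioning amounts to analysing the remaining 84.9 (75.5) per arm at 33%/53%, with power 75% (70%), so adjustment recovers only part of it. The documents give no prevalence for this goal, and their 33% can equally be read as the rate for everyone enrolled.

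**Conclusion.** The point holds as a weakness of method that should be corrected, not as a threat to validity. Covariates beyond site would be admitted on chance imbalance, with no defined trigger and no statement of which model then counts. At an assumed 0.05 trigger the rule captures 0 to 2 of the roughly 2 to 12 points of power available from prespecified adjustment, and it leaves open which odds ratio is reported.

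The size depends on assumed predictor strength. If only 5% of participants aim for a different sport, prespecifying that variable gains about 2 points. That the goal predicts the primary outcome follows from the outcome definition; how many participants hold it is unknown. The 43% chance of some trigger is illustrative only.

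**What to change.** Delete the sentence on rebalancing and the between-arm baseline comparison as a selection step; describe Table 3 by arm without tests. Before unblinding, fix the primary model as group, site and a short list of baseline variables already collected:

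- return-to-sport goal, whose relevance follows from the outcome definition;
- age, which the Eligibility criteria section names as an influence;
- desire to return, named in the same place. Table 3 has no item of that name; goal and expectations come nearest. The motivation questions are scheduled only at 3, 6 and 9 months, after allocation, and should not serve as a baseline covariate;
- others, such as the baseline K-SES future domain, by the team's judgement.

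State in advance how sparse cells are handled, for example by penalised logistic regression. With 188 analysed and 10% aiming for a different sport, about 19 participants have that goal; at the assumed 3% success rate the chance of no events among them is 0.97^19 = 56% (about 76% for 9 participants, 31% for 38). State that the adjusted odds ratio is conditional, and report the group-plus-site result as a sensitivity analysis.

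The cost is wording, slightly more analysis work, and a conditional in place of a marginal odds ratio. No new data are needed. About 94.35 × (0.33 + 0.53) = 81 primary events are expected, enough in total for a few added terms, apart from the sparse-cell issue.
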